### Interventions and follow up

Additional surgery involving the axilla after the results of SLNB are obtained in the control arm is dependent on the guideline of each treatment center. In both arms, adjuvant systemic therapy after surgery follows the guidelines of each center. Ipsilateral whole-breast radiation is mandatory for both arms. For the no-SLNB arm, the inclusion of axillary levels I and II within the tangential field or setting the upper margin of the field within 2 cm of the humeral head is recommended. The fractionation scheme follows 23–28 × 1.8–2.0 Gray (Gy) or 13–16 × 2.5–3.0 Gy. The boost to the tumor bed may be applied according to the policy of each center.

Follow-up of the patients will last for up to 5 years after surgery. The date of visit, status of disease progression, survival, adverse events, and quality of life findings will be reported at intervals of 3–6 months (according to each center’s policy). QoL questionnaires are acquired from the patients 1 and 2 years after the randomization using EORTC-BR23 and EORTC-QLQ-C30.

### Safety monitoring

In this study, we only gather adverse events related to axillary surgery according to the NCI/CTCAE v5.0 criteria followed by causality assessment. Severe adverse events should be reported to the primary investigator within 24 h of primary recognition of the event by the researcher. Severe adverse events should also be reported to the Institutional Review Board (IRB) within the timeframe designated by the IRB guidelines. Damages directly related with this trial to the subject that may occur during this clinical trial will be compensated in accordance with a clinical research agreement and insurance.

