**Methods:**

The NAUTILUS trial is a prospective multicenter randomized controlled trial involving clinical stage T1–2 and N0 breast cancer patients receiving breast-conserving surgery. Axillary ultrasound is mandatory before surgery with predefined imaging criteria for inclusion. Ultrasound-guided core needle biopsy or needle aspiration of a suspicious node is allowed. Patients will be randomized (1:1) into the no-SLNB (test) and SLNB (control) groups. A total of 1734 patients are needed, considering a 5% non-inferiority margin, 5% significance level, 80% statistical power, and 10% dropout rate. All patients in the two groups will receive ipsilateral whole-breast radiation according to a predefined protocol. The primary endpoint of this trial is the 5-year invasive disease-free survival. The secondary endpoints are overall survival, distant metastasis-free survival, axillary recurrence rate, and quality of life of the patients.

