### Screening and randomization

Participants undergo screening tests that will assess eligibility according to the inclusion/exclusion criteria. All procedures are performed after obtaining informed consent from the patients. Screening includes history taking, physical examination, pregnancy test, breast ultrasonography, and mammography. Additional tests can be performed if deemed necessary. AUS is performed by radiologists at each center to evaluate axillary lymph nodes. Written informed consent is obtained from each participant before enrollment by investigators. After enrollment, the randomization is conducted using a web-based system by investigators. Details of the randomization procedure will not be shared with the investigators of the clinical trial sites. The randomization table is prepared using SAS Version 9.4 (SAS Institute Inc., Cary, USA) with a stratified block randomization method. The stratification factors are treatment center and tumor size. The Medical Research Collaborating Center of Seoul National University Hospital (MRCC) created a random assignment table and operate it through web random assignment. Patients are blinded to their designated treatment arm before surgery to prevent bias or early dropout. During the randomization procedure, the investigator should provide the following information for each subject (protocol number, name of the clinical trial institution, screening number, tumor size). A randomization number is assigned through the web site, and a written confirmation of the subject is printed out and stored in the clinical trial basic document file provided to the institution. The randomization number applies to all case records and all subsequent correspondence related to the subject. Only pre-authorized investigators can access this randomization system.

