### Study outcomes

The primary endpoint is the 5-year invasive DFS, and the secondary endpoints are OS, distant metastasis-free survival, axillary recurrence rate, local recurrence rate, and self-reported adverse events. In addition, QoL will be evaluated twice at 1 year and 2 years after surgery. An interim analysis will be conducted after a 3-year follow-up.

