### Statistics

For nominal variables such as self-reported complications in each arm/group, the total number of patients, percentile, and frequency will be presented and analyzed using the chi-squared test or Fisher’s exact test. Continuous variables, such as age and tumor size, will be summarized using descriptive statistics (mean, standard deviation, median, etc.), followed by analysis using Student’s t-test or the Mann-Whitney U-test as a non-parametric test.

The statistical significance of the 5-year DFS, which is the primary endpoint, overall survival, and distant DFS will be determined using Kaplan-Meier analysis and the log-rank test. Cox proportional hazard regression analysis will be used to assess the prognostic significance of variables. For every statistical analysis, a *p*-value of < 0.05 will be considered statistically significant.

An interim analysis for the primary endpoint is planned once, and an interim analysis is performed 5 years from the date of IRB approval, and a final analysis is performed after at least 224 events have occurred. Disease-independent death is defined as a competing event. Fine and Gray regression is performed to verify the statistical hypothesis for comparison between groups, and the significance level used for interim and final analysis is calculated based on the O’Brien Fleming α-spending function, and the analysis uses SAS 9.4 Proc seq test.

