Eliminating or de-escalating axillary surgery aligns with the contemporary treatment trends. At least three clinical trials are being carried out, including the SOUND, INSEMA, and BOOG 2013–08 trials. The SOUND trial was designed to assess the non-inferiority of the 5-year distant DFS of cT1N0 breast cancer patients after SLNB to that after observation [19]. The INSEMA trial randomized cT1–2 N0 breast cancer patients into 4 groups, including the SLNB and SLNB-omission groups, and planned to analyze the 5-year DFS [20]. The BOOG 2013–08 trial also randomized cT1–2 N0 breast cancer patients into two groups, namely, the SLNB and no-SLNB groups, and evaluated the non-inferiority of regional recurrence in the no-SLNB group after 5- and 10-year follow-up [21]. These trials and our NAUTILUS trial altogether will answer the very important question that can alter the axillary surgery practice in breast cancer.

There are differences between this study and the aforementioned ongoing studies; however, this study has advantages. NAUTILUS is the only study targeting Asian breast cancer patients who are younger and more premenopausal than western women in terms of epidemiologic difference. Second, we have detailed ultrasonographic criteria for selecting patients and that is shared with breast radiologists (imaging) in each participating institution. Third, NAUTILUS aims to analyze the quality of life of each arm, which will add evidence to justify skipping SLNB. Cost-effectiveness will also be assessed for each arm.

In summary, the NAUTILUS trial aims to determine whether SLNB can be skipped for a specific breast cancer patient group. If there is no significant difference between the two randomized arms, patients who meet the criteria can have increased quality of life with less surgical morbidity and decreased medical costs but equivalent oncologic outcomes by avoiding unnecessary surgical procedures.

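### Adverse events are collected only if related to axillary surgery, which is planned in one arm only; read literally, arm and shoulder events are recorded unequally, in favour of no-SLNB

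*Protocol article*

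**What the plan says.** The collection rule is in the protocol article under Safety monitoring: "In this study, we only gather adverse events related to axillary surgery according to the NCI/CTCAE v5.0 criteria followed by causality assessment".

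The other statements that bear on it are:

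- **Arms** (Abstract, Methods): "Patients will be randomized (1:1) into the no-SLNB (test) and SLNB (control) groups".
- **Radiation** (Interventions and follow up): whole-breast radiation is mandatory in both arms. One recommendation is made for the test arm only. It begins "For the no-SLNB arm, the inclusion of axillary levels I and II within the tangential field" and offers as an alternative an upper field border no more than 2 cm from the humeral head.
- **Schedule** (same section): "The date of visit, status of disease progression, survival, adverse events, and quality of life findings will be reported at intervals of 3–6 months", with no distinction by arm. EORTC-BR23 and QLQ-C30 are taken at 1 and 2 years.
- **Endpoints** (Study outcomes): the secondary list ends with "axillary recurrence rate, local recurrence rate, and self-reported adverse events".
- **Analysis** (Statistics): "For nominal variables such as self-reported complications in each arm/group", counts and percentages are given and tested by chi-squared or Fisher's exact test.
- **Blinding** (Screening and randomization): "Patients are blinded to their designated treatment arm before surgery to prevent bias or early dropout". No blinding of those who assess adverse events is described.
- **Intended message** (Discussion): if the arms do not differ, eligible patients can have "less surgical morbidity and decreased medical costs but equivalent oncologic outcomes".

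**The concern.** A harm comparison between randomized arms needs the same events to be eligible for recording in both. Here eligibility is tied to attribution to a procedure that only one arm is planned to receive. Both arms have breast-conserving surgery and whole-breast radiation, so arm, shoulder and axillary symptoms can arise in either. If attribution decides what enters the database, the comparison partly measures the rule and not the patients.

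Two things are at stake. A difference in these events could not be read as the morbidity saved by omitting SLNB. And if the radiation field recommended for the no-SLNB arm did cause harm, that harm would not be counted, because it is not related to axillary surgery. Events that were never recorded cannot be restored at analysis.

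**Working it through.** The article gives no figure for adverse events, so there is none to reproduce. The check is a comparison of readings, followed by an illustration.

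**Step 1. What is recordable under each reading of the rule**

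| Event | Literal reading: relatedness is the condition for recording | Milder reading: axillary-type events are gathered, cause judged afterwards |
|---|---|---|
| Arm, shoulder or axillary event, SLNB arm | Recordable | Recordable |
| Same event, no-SLNB arm | Not recordable | Recordable |
| Same event caused by radiation, no-SLNB arm | Not recordable | Recordable |
| Radiation harm outside the axillary type, either arm | Not recordable | Not recordable |

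The second and third rows depend on the reading. The fourth does not.

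**Step 2. Who judges relatedness.** Patients are blinded only until surgery. Nobody can judge whether an event is related to axillary surgery without knowing whether it was performed. The judgement is therefore made with the arm known.

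**Step 3. Whether equal timing helps.** The 3- to 6-month schedule applies to both arms. It makes visit frequency comparable but does not change which events qualify at a visit.

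**Step 4. Illustration of the mechanism (not an estimate for this trial).** Let

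- p_C = rate in the SLNB arm, all recorded. I take 7.5%, the lymphedema incidence that the Background cites from an earlier sentinel-node trial.
- p_T = true rate in the no-SLNB arm (assumption).
- c = share of no-SLNB events that get recorded (assumption).

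True difference = p_C − p_T. Recorded difference = p_C − c × p_T. Bias = (1 − c) × p_T.

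| p_T | True difference | Recorded, c = 1 | Recorded, c = 0.25 | Recorded, c = 0 |
|---|---|---|---|---|
| 7.5% | 0 | 0 | 7.5 − 1.875 = 5.6 points | 7.5 points |
| 3.75% | 3.75 points | 3.75 points | 7.5 − 0.94 = 6.6 points | 7.5 points |
| 2% | 5.5 points | 5.5 points | 7.5 − 0.5 = 7.0 points | 7.5 points |

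In the first row there is no true difference. With the 780 per arm given under Sample size calculation, and c = 0.25, the standard error is √[(0.075 × 0.925 + 0.01875 × 0.98125)/780] = 0.0106. The ratio is 0.05625/0.0106 = 5.3, so a two-sided 5% test would be significant with probability near 1.00. At this sample size, unequal recording alone could produce a significant result.

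Both p_T and c are assumptions. The bias runs from 0 (c = 1, the milder reading followed consistently) up to p_T itself (c = 0), and the article fixes neither.

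**The case against.** The strongest case on the other side has four parts.

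1. **The rule may be milder than it looks.** If relatedness already decided what is collected, a later causality assessment would be largely redundant. A natural alternative is that collection is limited to the kinds of event that axillary surgery causes, with cause judged afterwards. The schedule, which makes no distinction by arm, fits this. This stands. A reader might infer that the no-SLNB arm scores near zero by definition, but that follows only on the literal reading. What remains is that the text does not choose between the two readings, and ten hospitals could apply it differently.

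2. **The rule may not govern the endpoint.** The secondary endpoint and the between-arm test concern self-reported events, and nothing says that these pass through the investigators' relatedness filter. The EORTC questionnaires carry no such filter. This also stands. A reader might infer that the trial's whole morbidity comparison is biased; the article does not support that. The questionnaires are not a full substitute, however. They are taken at 1 and 2 years, while the Discussion cites numbness and tingling that peak at 6 months and arm-volume differences at 36 months, and they are not CTCAE-graded.

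3. **Radiation harm is conjecture.** The recommendation has two alternatives, only one of which names levels I and II, and the article makes no such statement for the control arm's field. So extra harm in the no-SLNB arm is not shown. The point is only that, on the literal reading, such harm could not be recorded if it occurred.

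4. **The event list may be in the full protocol.** A checklist is the kind of detail that an article leaves out, and its absence is no finding. But the article does state a collection rule, with the word *only*, and that rule is what needs correcting.

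**Conclusion.** The point holds in a limited form. As written, the rule ties recording to a procedure planned in one arm and to a judgement made with the arm known. Read literally, it gives unequal ascertainment of arm, shoulder and axillary events, and any between-arm comparison of these investigator-collected events would favour no-SLNB. On the milder reading that imbalance can disappear, but radiation harms outside the axillary type are still left out.

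The direction of the bias follows from the text; its size does not. A reader might set the 8% arm-volume figure quoted in the Discussion against 0% and call the gap the bias. The article does not support this: the 8% comes from another trial, no arm-volume measurement is described here, and the 0% presupposes the literal reading. Nor does the article make reduced morbidity a main pillar of the trial. Its stated primary aim is oncologic safety, and the Discussion sentence on morbidity is conditional.

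The primary endpoint, the sample size and the EORTC questionnaires are not affected. Severity is moderate: a secondary safety outcome, with a cheap remedy.

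**What to change.** Replace the collection rule under Safety monitoring with one that does not depend on attribution, for example:

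> *In both arms, at every scheduled follow-up visit, a fixed list of arm, shoulder, axillary and breast or chest-wall events is recorded and graded by CTCAE v5.0, whatever the attributed cause. Arms are compared on all recorded events. Causality is reported descriptively only.*

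The list should cover at least lymphedema, pain, numbness or paresthesia, limited shoulder movement, seroma or infection, and radiation-related events. The section should also say whether the self-reported adverse events follow the same rule.

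The cost is a checklist on the case report form and slightly more data entry. The visits every 3 to 6 months already exist. The change should be made while data are still being collected. If the literal reading has been in use, the report should say from which date the new rule applied, since earlier unrecorded events cannot be recovered.

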### Study outcomes

The primary endpoint is the 5-year invasive DFS, and the secondary endpoints are OS, distant metastasis-free survival, axillary recurrence rate, local recurrence rate, and self-reported adverse events. In addition, QoL will be evaluated twice at 1 year and 2 years after surgery. An interim analysis will be conducted after a 3-year follow-up.

### Data management and monitoring

Principal Investigator has full responsibility of entire projects of this trial. Clinical Research Organization (CRO) has roles of the coordinating center, CRO will help each hospitals which can proceed trial more effectively and will perform data monitoring and coordinate meetings of investigators. During patient recruitment monitoring on site is performed according to good clinical practice (GCP) guidelines. MRCC will perform data management team with data monitoring plan (DMP).

Data monitoring will be performed by CRO and clinical research coordinator (CRC) of each hospital and principal investigator will monitor entire data. In-house monitoring will be performed regularly with needs of investigators. Routine monitoring will be performed about 20 times with CRO and principal investigator.

All documents related to this clinical trial should be kept at the clinical trial institution. Subject (hospital or medical records) files are kept in accordance with domestic regulations. All documents related to this trial must be kept for 3 years after the end of the study. At the end of this period, the investigator obtains written approval from the trial coordinator before discarding the document. If a subject withdraws consent while participating in a clinical trial, data after the time of withdrawal of consent will not be collected. Research-related anonymized data and documents collected before the withdrawal of consent are retained and used for up to 3 years after the end of the study, and the investigator obtains written approval from the clinical trial coordinator of this study before discarding the documents when this period ends.

### Statistics

For nominal variables such as self-reported complications in each arm/group, the total number of patients, percentile, and frequency will be presented and analyzed using the chi-squared test or Fisher’s exact test. Continuous variables, such as age and tumor size, will be summarized using descriptive statistics (mean, standard deviation, median, etc.), followed by analysis using Student’s t-test or the Mann-Whitney U-test as a non-parametric test.

The statistical significance of the 5-year DFS, which is the primary endpoint, overall survival, and distant DFS will be determined using Kaplan-Meier analysis and the log-rank test. Cox proportional hazard regression analysis will be used to assess the prognostic significance of variables. For every statistical analysis, a *p*-value of < 0.05 will be considered statistically significant.

An interim analysis for the primary endpoint is planned once, and an interim analysis is performed 5 years from the date of IRB approval, and a final analysis is performed after at least 224 events have occurred. Disease-independent death is defined as a competing event. Fine and Gray regression is performed to verify the statistical hypothesis for comparison between groups, and the significance level used for interim and final analysis is calculated based on the O’Brien Fleming α-spending function, and the analysis uses SAS 9.4 Proc seq test.

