The axillary lymph node status became less important for deciding on adjuvant therapies for early breast cancer. In human epidermal growth factor receptor 2 (HER2)-positive or triple-negative breast cancers, adjuvant chemotherapy and/or HER2 targeted therapy was indicated regardless of lymph node status. For estrogen-receptor-positive HER2-negative breast cancers, multigene assays, such as the 21-gene or 70-gene assay, are used to guide adjuvant chemotherapy decisions.

With advances in imaging techniques, the accuracy of presurgical lymph node status prediction based on axillary ultrasonography (AUS) with or without core biopsy or fine-needle aspiration (FNA) has increased significantly. In a study by Cho et al., sonographic classification of axillary lymph nodes showed 85% sensitivity and 78% specificity for predicting metastasis when a cutoff for cortical thickness of 2.5 mm was used [7]. In the SOUND trial, preoperative AUS resulted in 15.5% of FNR, which was reduced to 8.1%, excluding isolated tumor cells and micrometastases, and 4.9%, considering only metastases of > 3 mm, which are the only lesions that AUS can reliably detect. The NPV was 95% after excluding isolated tumor cells and micrometastases [8].

Taking everything into consideration, this clinical trial aims to show whether SLNB can be omitted in a specific patient group. If there is no significant difference between the SLNB and non-SLNB groups, patients would have increased quality of life by eliminating unnecessary surgical procedures.

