### Sample size calculation

We designed the NAUTILUS study to determine whether the no-SLNB group was not inferior to the standard SLNB group. In the NSABP B-32 study, the 5-year DFS was 88.6% for cT1–2 N0 breast cancer [2]. We assumed that the DFS of our study patients would be lower than this because lymph node-positive patients will be included in our study. In the ACOSOG Z0011 study, the 5-year DFS was 83.9% for cT1–2 N1 (1 or 2 lymph node-positive) [6]. We assumed that the DFS of our study patients would be higher than this. As a result, the expected 5-year DFS of the control group of our study is 86%.

The 5% non-inferiority margin, 80% power, 5% two-sided significance level resulted in a sample size of 780 per study arm. Assuming a 10% dropout rate, 1734 patients need to be randomized. Patients are recruited competitively from each institution.

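### The trial is designed for non-inferiority with a 5-point margin, but no stated analysis compares the result with that margin, and non-significance is read as grounds to omit SLNB

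*Protocol article*

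**What the plan says.** The Abstract and the Sample size calculation section describe a non-inferiority trial. The latter says the aim is "to determine whether the no-SLNB group was not inferior to the standard SLNB group", takes 86% as the control arm's 5-year DFS, and reports: "The 5% non-inferiority margin, 80% power, 5% two-sided significance level resulted in a sample size of 780 per study arm". It continues: "Assuming a 10% dropout rate, 1734 patients need to be randomized".

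The Statistics section names two analyses for the primary endpoint:

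- The significance of 5-year DFS, "which is the primary endpoint, overall survival, and distant DFS will be determined using Kaplan-Meier analysis and the log-rank test". A p-value below 0.05 counts as significant in every analysis.
- In the last paragraph, Fine and Gray regression is given the task of testing the hypothesis between arms, with disease-independent death as a competing event. There is one interim look with O'Brien-Fleming spending, and the final analysis needs at least 224 events.

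Neither mentions the margin, a shifted null hypothesis or a confidence-limit rule.

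Two other places say how the result will be read. The Background has: "If there is no significant difference between the SLNB and non-SLNB groups, patients would have increased quality of life". The Discussion has: "If there is no significant difference between the two randomized arms, patients who meet the criteria can have increased quality of life", and the same sentence goes on to describe the oncological outcomes as equivalent.

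**The concern.** A log-rank test at p < 0.05 asks whether the arms differ. Failing to show a difference does not show that any loss is smaller than 5 points. The fewer the events, the easier a non-significant result becomes, so the reading in the Background and Discussion makes the favourable conclusion more likely as information is lost. The trial is meant to show that leaving out an operation is safe, so this error falls on the patient's side.

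The Fine and Gray sentence does not settle the matter. It carries no margin. With disease-independent death as a competing event, it estimates a subdistribution hazard ratio, which is not the 5-point difference in 5-year DFS used to size the trial. The section also does not say whether this regression or the log-rank test decides the primary question.

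**Working it through.** **Inputs.** From the Sample size calculation section: control 5-year DFS 86%, margin 5 points (so 81% at the margin), two-sided 5% level, 80% power, 780 per arm, 10% dropout. From the Statistics section: 224 events. Assumed here: exponential DFS, proportional hazards, 5 years of follow-up for each patient, and no adjustment for competing risks or the interim look.

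**Reproducing the plan's size.** For a non-inferiority test of two proportions, both truly 86%, at one-sided 2.5%:

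n = (1.960 + 0.842)² × 2 × 0.86 × 0.14 / 0.05² ≈ 757 per arm.

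The stated 780 is within 3% of this. One-sided 5% would give 596, which does not match. For dropout, 780 / 0.90 rounds up to 867, and 2 × 867 = 1734, exactly as stated. The sample size therefore fits a margin-based test at one-sided 2.5%.

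**Hazard ratio at the margin.** ln(0.81) / ln(0.86) = 1.397.

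**Chance that an arm exactly 5 points worse gives a non-significant result.** For D events, the log-rank test gives

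1 − Φ( √(D/4) × ln 1.397 − 1.96 ).

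Expected events are 780 × (0.14 + 0.19) = 257.4 at 780 per arm, and 867 × 0.33 = 286.1 if every randomised patient is followed.

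| Basis | P(non-significant) |
|---|---|
| Two proportions, 780 per arm | 24.1% |
| Log-rank, 257 events | 23.5% |
| Log-rank simulation, 780 per arm | 24.8% |
| Log-rank, 224 events | 29.4% |
| Two proportions, 867 per arm | 19.9% |
| Log-rank, 286 events | 19.3% |
| Log-rank simulation, 867 per arm | 19.7% |

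A rule that requires the two-sided 95% confidence interval to exclude a 5-point loss holds this error at 2.5% by construction.

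**The two rules in terms of observed loss.** At 780 per arm with both arms near 86%, SE = √(2 × 0.86 × 0.14 / 780) = 1.757 points. The margin rule passes an observed loss below 5 − 1.96 × 1.757 ≈ 1.6 points. The non-significance rule passes losses up to 1.96 × 1.757 ≈ 3.4 points.

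**The event trigger.** With a hazard-ratio margin of 1.397 and 80% power, one-sided 5% needs 222 (Schoenfeld) or 226 (Freedman) events. One-sided 2.5%, which matches the stated two-sided 5%, needs 281 or 286. The stated 224 fits the former.

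**The case against.** A reader might infer that the non-inferiority hypothesis is not tested at all and that a log-rank p-value alone decides the trial. The document does not support that. The last paragraph of the Statistics section assigns the hypothesis to Fine and Gray regression, and the log-rank sentence is a general one that also covers overall survival and distant DFS. The 224 events lie close to a margin-based calculation at one-sided 5%. A margin on a hazard scale may therefore be intended and set out in a full protocol or analysis plan that is not shown, and an article may leave such detail there. Also, the sentences in the Background and Discussion are narrative about hoped-for benefits and are not labelled as decision rules.

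This narrows the point but does not remove it. The point is about what the article does state: a test, a threshold and an interpretation that do not fit the hypothesis. The interpretation appears twice. The 224 events cannot stand in for a stated margin, because they do not agree with the two-sided 5% level used for the sample size.

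Two further inferences fail:

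- That a small significant loss inside the margin would wrongly be called a failure. At 780 per arm, significance needs an observed loss above about 3.4 points and non-inferiority needs one below about 1.6, so such a result would fail the margin rule too.
- That crossover is a special weakness of the non-significance reading. Crossover dilutes differences and favours a margin-based test as well.

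**Conclusion.** The point holds in this form: the design has a 5-point margin, no analysis stated in the Statistics section compares the result with it, two primary analyses are left unreconciled, and the Background and Discussion read non-significance as grounds for omission. It should be corrected before the final analysis, because it concerns the rule for the main conclusion.

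The size is conditional. If non-significance is taken as proof of safety and the true loss equals the margin, the wrong conclusion follows about 24% of the time at 780 per arm, with a range of about 19% to 29% according to patients followed or events, against 2.5% for a margin-based test. The figures assume proportional hazards and ignore the interim adjustment; a final significance level below 5% would make non-significance somewhat more likely. They are not the trial's error rate if a margin-based test in an unseen document in fact governs.

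**What to change.** In the Statistics section, name one primary test that uses the margin. Either of these would do:

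- The difference in Kaplan-Meier 5-year invasive DFS (no-SLNB minus SLNB) with a two-sided 95% confidence interval adjusted for the interim look. Non-inferiority is declared only if the lower limit is above −5 points. This matches the sample size: at 780 per arm and 86% in both arms, power before the interim adjustment is about 81%.
- A pre-stated hazard-ratio margin of about 1.40, which suits an event trigger. The level must then be settled: 224 events give 80.4% power at one-sided 5% but 70.6% at one-sided 2.5%.

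Make the log-rank test and the Fine and Gray regression secondary or descriptive, or state how the latter carries the margin. Replace the non-significance sentences in the Background and Discussion with the chosen rule.

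The first option costs only protocol and analysis-plan wording, with no added patients or data. The second also needs the event count and significance level to be reconciled.
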